#### Implementation

After the health care workers were trained in the intervention group’s health centers, supervisions were organized throughout the data collection period to verify the implementation of the intervention.

#### Blinding

Given our intervention’s nature, blinding the participants and the research team was impossible.

### Data Collection Methods

Data collectors were trained before the inclusion of participants on all the procedures of inclusion, follow-up, and how data must be collected (data sources). They were not health care workers. Therefore, the study procedures were standardized across all sites. Data were collected from women on the day of inclusion and at each successive ANC, up to the sixth week after delivery. One data collector was assigned to 2 neighboring health centers for the duration of the study (1 intervention group health center and 1 comparison group health center). The questionnaires were administered to the participants immediately after the antenatal visit, after the delivery, and after each postpartum visit. The interviewer visited the health center according to the ANC schedule. A field coordinator was recruited and responsible for checking all the data collection steps, including the recruitment of participants.

The participant’s knowledge was measured at the study inclusion and at the end of pregnancy. This knowledge covered topics such as the danger signs of pregnancy, signs of labor starting, danger signs after childbirth for the woman, and newborn’s danger signs. All these signs are normally discussed with the woman at each ANC visit to improve her knowledge to stimulate early consultation if any one of the following signs occur:

Danger signs of pregnancy: vaginal bleeding, fever, intense intractable headache, difficulty breathing, convulsions and loss of consciousness, intense abdominal pain, non–bloody vaginal discharge, lack of fetal movement, and feet and hands edema.Signs of the onset of labor: loss of water, painful and regular contractions, and discharge of red and viscous mucus.Newborn danger signs: fever, hypothermia, convulsions, inability to breastfeed, vomiting, pus or bleeding from the cord, purulent discharge from the eyes, jaundice, hypotonia, unexplained crying, abdominal pain, bloating, diarrhea, and difficulty breathing.Danger signs after childbirth for the woman: convulsions, heavy vaginal bleeding, intense abdominal pain, intense headaches, dizziness, rapid or difficult breathing, fever, bad odor discharge from the vulva, and paleness of the mucous membranes.

For each group of signs, there was a proportion of women who knew no signs and a proportion of women who knew at least 3 signs. Furthermore, we measured women’s birth preparedness by asking the woman if she had identified a health facility for her delivery or in case of emergency, if she had identified a companion of choice for labor and childbirth, or in case of emergency, if she had planned the financing of the main expenses related to her delivery and if she had identified one means of transport to reach the health facility for the delivery. Those who took precautions for each of the 4 questions scored 1 for each question and 0 if the woman took no precautions. The use of maternal and child health services was measured by the number of ANC visits attended by the woman, place of delivery, postnatal consultation on days 6-10, and postnatal consultation in 6-8 weeks. The different variables with their measurement periods are presented in Figure 3.

**Figure 3 figure3:**
[figure not shown]
Schedule of participants' enrollment, allocation, interventions, and assessments in the randomized controlled trial. ANC: antenatal care; PANDA: Pregnancy and Newborn Diagnostic Assessment.

For this study, data were collected using a closed questionnaire by directly interviewing the women and extracting data from ANC registers, delivery registers, ANC cards, and health care records. To understand the satisfaction of pregnant women, we use a satisfaction scale consisting of very satisfied, satisfied, neutral, not very satisfied, and not at all satisfied, which will be rated as 4, 3, 2, 1, and 0, respectively. The data collector explained to the woman that she is free to give the number of green stars corresponding to her satisfaction level for each subitem listed in Textbox 1 below. The image is shown and explained to the woman in order to rate her satisfaction. The number of green stars chosen correspond to her level of satisfaction with that subitem. The maximum score for each subitem is 4 and the minimum is 0. This satisfaction was measured at each antenatal visit for each woman enrolled in the research. It should be recalled that the data collectors were women without health care training who were recruited and assigned to each health center. Data collectors did not interfere in the care relationship with the women.

Items and subitems for measuring the satisfaction of pregnant women.
**Women’s satisfaction with interpersonal relations with staff (5 subitems)**
WelcomingRespecting the confidentiality of consultation with the health care providerRespecting privacy during consultationRespect and courtesy of the health care providers during antenatal careGoodbye from staff
**Quality of service (9 subitems)**
Waiting timeOverall time spent in the health centerOther times to wait for test resultsHealth care provider skillsExplanation of iron–folic acid dosingExplanation of malarial prophylaxisExplanation of preventive measures against malariaExplanation of women’s dietExplanation of different complementary examinations

### Data Management

Data collection was performed electronically by using tablets. Only the identifying information of the participants was collected on paper to maintain the anonymity of the women in the different databases. In both groups, registers, health records, ANC cards, and women’s self-report were used for data collection. We developed a data quality assurance plan for the duration of the trial. Implementation was under the supervision of the research team. Confidentiality of the data was ensured by protecting devices with passwords kept in a secure location. A data entry program was developed using the CSEntry Android app of Census and Survey Processing System software [30]. The data manager exported the data to Stata 15.1 for correction and use. We implemented the following measures to ensure effective data management:

The information collected during the various contacts with women was verified several times at different levels. Data collectors were responsible for ensuring that all data collected were accurate. They reviewed all the completed forms before uploading them to the server to guarantee completeness and resolve inconsistencies.All data were stored on a server compatible with good clinical practice, and data transmission will be encrypted to ensure data integrity and patient confidentiality. The access to data management was password protected, and only authorized users had access.

### Statistical Methods

Quantitative data were extracted and transferred to Stata 15.1 for analysis. We will perform an intention-to-treat and per-protocol analysis of the cluster randomized trial. The unit of analysis will be women. The analysis will compare the intervention and comparison groups’ unadjusted and adjusted primary outcomes results. Unbalanced factors between the 2 study groups will be used to adjust the intervention effects on the study outcomes. These factors will be women’s sociodemographic factors and women’s autonomy. The means and proportion comparison tests for independent samples will be used at the 5% threshold. In case of nonnormality of a quantitative variable (satisfaction scores, knowledge scores, etc), robust or Poisson regression will be used.

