#### Sample Size

In addition to the desired statistical power and percentage of potential lost to follow-up, the calculation of the required size considered several statistical features inherent to the design of the study, such as the number of participants per cluster, the intraclass correlation coefficient (ICC), and the inflation factor [24-27]:

Number of participants: To be practical and comfortable with data collection, we considered 40 women per health center, excluding those lost to follow-up.ICC: This measures the extent of the cluster effect and assesses the degree of similarity between the individuals within a cluster. It is based on the relationship between the intercluster variance and the intracluster variance. For this reason, the sample sizes must be increased to account for the clustering effect. In particular, the value of ICC depends on the unit of randomization and the type of outcome. In our case, we have women likely to come from the rural areas of several health zones. Given the composition of health care workers in rural health centers (midwives and birth attendants), it is reasonable to assume that there will be slight variations between women moving from one health center to another. For this, we propose an ICC of 0.015.Inflation factor: The increase required to account for the cluster effect is influenced by ICC and cluster size. The standard sample size was increased by an inflation factor equal to [1 + (n – 1) ρ], where n is the average cluster size and ρ is the estimated ICC. By numerical application, inflation factor = 1.585.The desired statistical power was 80%.The margin of error was 5%.The estimated proportion of those lost to follow-up was set to 10%.

Using Stata 15.1 software [28], health centers needed to detect a difference of at least 15% (80% in the intervention group vs 65% in the control group) in the proportion of women with an excellent ANC quality score in 6 health centers in each group. Considering the loss to follow-up proportion at 10%, the minimum final size required is 264 women in each group with 12 health centers, except the urban health facility. The hypothetical proportion of 65% in the comparison group was derived from a study conducted in Ghana in 2019 by Baafi et al [29].

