#### Randomization

Facilities were randomized using a matched-pair method. Health centers were selected by identifying 6 pairs of comparable health centers. The matching criteria were (1) number of total ANC visits in the year before the trial, (2) number of total deliveries in the year before the trial, (3) number of total postnatal care visits in the year before the trial, (4) number of women of childbearing age in the health center area, (5) total number of health care workers in the health center as well as the distribution by profile (midwives, nurses, and auxiliary birth attendants), and (6) size of the population served. These matching variables allow us to obtain facilities within each pair that are similar to each other regarding these matching factors. Within each pair, the center that received the PANDA app was chosen randomly using the draw of 1 health center from each pair; the names of the health centers were previously arranged in individual envelopes and sealed. The drawer was different from the one who prepared the envelopes and did not attend the sealing. The draw, therefore, was carried out 6 times. All consecutive and eligible participants were included in the clusters.

To assess women in the semiurban environment (city of Koupéla), we included the health center in Koupéla, which unfortunately could not be matched to another city, given its size and characteristics. To minimize the likelihood of cross-group contamination, facilities are chosen to ensure they are far enough apart. Moreover, women generally did not move from one center to another due to the distance between the health centers. They usually visit the same health center for ANC during their pregnancy. We included only the women who were sure they would realize all their ANC visits in the health center where they were included in this study. Lastly, no staff move was noted during the study between the 2 arms. The health centers selected as the study sites are shown in Table 2.

**Table 2 table2:** Study sites.

	Health center
Pair 1	Baskouré and Kalwêga
Pair 2	Boangtenga and Zaogo
Pair 3	Dialgaye and Yargo
Pair 4	Baadtenga and Sampongho
Pair 5	Gounghin and Ligdi-Malguem
Pair 6	Kabéga and Zéguédéga
One semiurban center	Koupéla health center

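### The named tests treat women as independent although health centers were randomized in pairs; at the plan's own ICC a nominal 5% test has a true error of about 12–14%, or about 7–12% if the matching worked

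*Protocol article*

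**What the plan says.** The Randomization section of the protocol article says "Facilities were randomized using a matched-pair method": six pairs of centers, one draw per pair. A thirteenth center, Koupéla, was added outside the draws; it is the one "which unfortunately could not be matched to another city, given its size and characteristics".

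The Sample Size section assumes 40 women per center and an ICC of 0.015, and multiplies the individual-level sample size accordingly: "By numerical application, inflation factor = 1.585". It arrives at 6 centers and 264 women per group, not counting the urban center.

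The Statistical Methods section then says "The unit of analysis will be women" and "The means and proportion comparison tests for independent samples will be used at the 5% threshold". It promises unadjusted and adjusted results for the primary outcome, adjusting for factors found to be unbalanced: "These factors will be women’s sociodemographic factors and women’s autonomy". The only model it names is a fallback: "In case of nonnormality of a quantitative variable (satisfaction scores, knowledge scores, etc), robust or Poisson regression will be used".

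**The concern.** Women at one center share staff, equipment and habits of care, and the allocation was made for the center as a whole. The sample-size section recognizes this and pays for it. The analysis section does not: a two-sample test on individual women computes its standard error as if each woman had been allocated separately.

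Nothing else in the section repairs this. The adjustment factors are all characteristics of the woman. The robust or Poisson fallback is triggered by nonnormality of a quantitative variable, so it does not reach the binary primary outcome and says nothing about centers. Calling the trial cluster randomized in the same paragraph labels the design without supplying a method.

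The standard error of the unadjusted comparison is therefore too small, its interval too narrow and its p-value too low. With six or seven centers per arm, a few well-run centers on one side could yield a significant difference without any effect of PANDA.

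**Working it through.** **Inputs.** From Sample Size: 40 women per center, ICC 0.015, 80% against 65%, power 80%, 5% error, 10% loss. From the Abstract: 423 and 272 women enrolled in 13 centers. The 7/6 split of centers is inferred from the qualitative section, which counts 7 centers on the PANDA side, including the semiurban one.

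**1. The plan's own figures.**
- Inflation: 1 + (40 − 1) × 0.015 = 1.585.
- Two-sided comparison of 80% with 65%: 138 women per arm, or 151 with continuity correction.
- 138 × 1.585 = 218.7, and 218.7 / 40 = 5.47. With correction, 151 × 1.585 = 239.3, and 239.3 / 40 = 5.98. Both round up to 6 centers.
- 6 × 40 = 240, and 240 × 1.10 = 264.

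All three stated figures are reproduced. The article does not state sidedness, but a one-sided calculation would need only 5 centers (109 × 1.585 / 40 = 4.32; 122 × 1.585 / 40 = 4.83), so two-sided is the natural reading.

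**2. True error of a test that ignores clustering.** If the true variance is D times the variance the test uses, the error is 2 × (1 − Φ(1.96/√D)).
- Planned sizes: D = 1.585 and 1.96/1.259 = 1.557, giving **12.0%**.
- Enrolled sizes, equal within arm: 423/7 = 60.4 gives 1 + 59.4 × 0.015 = 1.891, and 272/6 = 45.3 gives 1 + 44.3 × 0.015 = 1.665. Then D = (1.891/423 + 1.665/272) / (1/423 + 1/272) = 1.754, giving **13.9%**.

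A beta-binomial simulation (100,000 replicates, proportion 65%) gives 12.1% and 13.9%.

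**3. Allowing for the matching.** Between-center variance shared within a pair cancels in the arm difference. If pairing removes a share f of it, then at 40 women per center D = 1.585 − 40 × 0.015 × f = 1.585 − 0.6f. The simulated errors are:

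| Share removed by pairing (assumed) | Planned sizes | Enrolled sizes |
|---|---|---|
| 0% | 12.1% | 13.9% |
| 25% | 10.4% | 12.0% |
| 50% | 8.5% | 9.8% |
| 75% | 6.7% | 7.7% |

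**4. Factors that raise it** (no matching gain; all values assumed). If Koupéla supplied 150 to 200 of the 423 women, the error is about 15% to 17%. At an ICC of 0.03 it is 18% (planned) or 22% (enrolled), and at 0.05 it is 25% or 30%. At an ICC of 0.005 it falls to 7% or 8%.

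**5. Power of a valid analysis.** With 240 women per arm, the standard error of the difference is √((0.80 × 0.20 + 0.65 × 0.35) × 1.585 / 240) = 0.0506, and 0.15 / 0.0506 = 2.97. The normal approximation gives 84% power. A cluster-level t test gives 76% on 10 df (unpaired) and 66% on 5 df (paired, no matching gain).

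**The case against.** The strongest reply is that the 12–14% gives no credit to the matching. Centers were paired on six criteria, and an unpaired test is less liberal when pairing succeeds. This stands: the figure holds only with no matching gain, which is also how the plan's own inflation factor is built. It has to be given alongside the 7–12% range.

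A second reply is that an article may leave analysis detail to a fuller plan, and that independent samples may mean only two-sample. Neither removes the problem. A test is named, the woman is its unit and no cluster term accompanies it, so a fuller plan must either repeat the error or contradict the article.

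Three stronger readings are tempting but not supported.
- A reader might infer that every analysis, including the adjusted one, ignores centers. No model is named for the adjusted comparison; what is stated wrongly is the two-sample testing. The adjusted analysis needs the same repair because its listed covariates include no center or pair term, but its form is unstated.
- A reader might infer from "This satisfaction was measured at each antenatal visit for each woman enrolled in the research" that visits will be pooled as independent records. The article does not say so. A per-visit, last-visit or averaged score is equally compatible.
- A reader might object to Poisson regression for a satisfaction item rated 0 to 4. The fallback concerns satisfaction and knowledge scores, satisfaction has 14 subitems, and nothing says that single items will be modeled. The choice of distribution is in any case separate from clustering.

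**Conclusion.** The concern holds for the tests as written. They are wrong for a trial that randomized centers, and they contradict the article's own sample-size section. The size depends on assumptions that should travel with it: two-sided testing, ICC 0.015, a 7/6 split and equal center sizes within arm. On those, the true error of the nominal 5% test is about 12% (planned) to 14% (enrolled) with no matching gain. It is about 7–12% if pairing removed 75% to 25% of the between-center variance, and higher with unequal centers or a larger ICC. At the plan's ICC it returns to about 5% only if pairing removed almost all of that variance, which the article neither claims nor uses.

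A reader might go further and infer that any positive result of this trial is a center effect. The article reports no outcome results and does not show what was actually run, so it supports only the conclusion that the stated test cannot rule this out at the 5% level.

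**What to change.** Replace the sentence on independent-sample tests with an analysis that respects the randomized centers and carries a small-sample correction, for both the unadjusted and the adjusted comparison. Any of these would do, provided one is named as primary:
- a t test on center proportions (covariate-adjusted residuals for the adjusted version), paired on 5 df or unpaired on 10 df for the 12 randomized centers;
- a mixed model or GEE with center as the cluster and a small-sample correction.

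An exact permutation test over the 2^6 = 64 possible allocations can serve as a check; its smallest two-sided p-value is 2/64 = 0.031.

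State how Koupéla is handled. It was outside the six draws and outside the 12 centers of the sample size, so keep it out of the randomized primary comparison and report it in a sensitivity analysis. Leaving it out does not breach intention-to-treat for the randomized centers, but it must be said openly.

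**Cost.** No new data are needed. Intervals will be wider, and power at planned sizes falls to the 76% or 66% shown above, so the choice between unpaired and paired should be justified. The Results section says analysis finished in June 2023, so the change must be reported as made after the analysis, with the results of the replaced tests shown beside the new ones.

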### Data Monitoring

Since the participants were not given an experimental drug, we did not conduct an interim analysis to determine whether to stop. The team was supervised every month. The management focused on aspects such as the quality of the collected data, careful adherence to every step of the protocol and validated methods, and using the PANDA app. In addition, monthly meetings were held online with all technical and financial partners to resolve difficulties. The supervision and meeting reports were produced and archived systematically.

### Ethics Approval

This trial was retrospectively registered with the Pan-African Clinical Trials Registry under PACTR202009861550402 on September 21, 2020. The Burkina Faso Health Research ethics committee approved the research protocol for this trial under approval 2020-3-051. This study does not introduce any new drug treatments. The PANDA system was designed by the standards and protocols in force in Burkina Faso. Any problems identified will be managed according to the procedures and practices in the health system. Adult participants (at least 18 years old) were included after obtaining their informed consent. Minor participants were included by obtaining their assent and parental consent. In the case of minor participants, informed consent of the parent or the respective legal guardian was obtained in conjunction with informed permission of the underage participant (younger than 18 years). The interviewers assigned to the various health centers were responsible for obtaining consent. This process was carefully checked during the field supervision of the research team. All questionnaires in the database did not contain any information that could be used to identify a woman formally. The participants’ phone numbers and identities were recorded in a physical document, allowing the interviewer to locate the woman, if necessary, to administer a questionnaire.

### Qualitative Analysis of Factors Hindering or Facilitating Implementation

We conducted a qualitative evaluation of the implementation of the PANDA system to identify the interactions (positive or negative) between the intervention and the implementation environment. The target population comprised the intervention group and the resource personnel. The intervention group included women who had recently given birth, providers of the health centers where the PANDA system was used, and resource persons. With women, we measured mainly their perceptions of the quality of care and interactions with health providers. The health care providers were interviewed to give their opinion about the PANDA system’s technical aspects, interactions with women, and perceptions of the quality of the medical procedures provided. Given their positions in this research, the resource persons were the key informants. They were the district management team, managers of the medical unit, Directorate of Health Information Systems, Directorate of Family Health, and members of 2 nongovernmental organizations, namely, Enfants du Monde, Switzerland, and the Private and Community Initiative for Health and the Response to HIV/AIDS in Burkina Faso.

Following the reasoned approach, we performed 4 focus groups with women who had recently given birth (1 focus group per center in 4 health centers), 22 in-depth individual interviews, and again with women who had recently given birth in the 7 health centers (3 interviews per center); 18 in-depth individual interviews were conducted with the health workers of the 7 health centers (2 per center, including the medical unit). However, given the size of the CSPS Urbain (the only semiurban center), the number of health workers interviewed was 4. We also conducted 4 in-depth individual interviews with the technical and financial partners. In total, 44 individual interviews and 4 focus groups were performed.

The qualitative component used the semistructured interview [31]. The women were recruited in a reasoned manner from among those included in the study—mainly the last women enrolled in this study to give birth to guarantee the freshness of memory. In addition to the primary data, secondary data were collected through activity reports (training missions since the beginning, supervision missions conducted by the research team, etc), budgets allocated to program activities, national health policy documents, PANDA app user guide, etc. The explored themes were as follows: the satisfaction of the participants in the intervention group, the acceptability of the intervention to health care workers, and the barriers and catalysts for an efficient and effective implementation of the PANDA system.

Content analysis [32] was used as the data processing and analysis technique. The digitally collected data were transcribed into French and entered into Microsoft Word. The transcribed data were analyzed thematically using a manual approach with the help of analysis tables. The analysis model used was the strengths-weaknesses-opportunities-threats model. It enabled us to identify the interactions (positive or negative) between the intervention on the one hand and the implementation environment on the other. These diversions will allow us to consider the necessary readjustments for greater efficiency and effectiveness of the intervention.

